### Outcomes to be measured

This exploratory Wellcome Trust funded Seed Award in Science research in four districts of Nepal will:
i. characterise social determinants of TB by comparing poverty level, education level, food security, and other socioeconomic factors of people with TB (Cases) versus people without TB (Controls);ii. provide new insight into the barriers, facilitators, and socioeconomic impact of being ill with TB and accessing TB diagnosis and care, and compare this in Cases diagnosed by ACF versus PCF; andiii. generate a community-led shortlist of the most feasible, equitable, and locally-appropriate socioeconomic interventions for TB-affected households to mitigate the socioeconomic impact of TB.

### Data collection and management

During the implementation of Project 1, information will be collected by BNMT district coordinators, community volunteers, and community mobilisers with support from the project team during visits to recruited patient households. This information includes but is not limited to socioeconomic, health, psychosocial, and behavioural data. This data will be collected on paper due to digital collection (e.g. on tablets or mobile phones) having issues with security and feasibility. The data of consenting TB patients will subsequently be linked with data from NTP’s TB patient register as part of its routine surveillance data collection at the intervention and control areas, with pre-existing permission from the NTP.

During Project 2, key stakeholders identified by the scoping exercise will complete a short pre-FGD survey in person, participate in an FGD, and participate in a one-day workshop.

All paper-based copies, including medical records, informed consent forms and participant information leaflets, will contain only a unique study identifier for each participant. These documents will be stored in a locked room in the BNMT office. Data will be checked for consistency and completeness by the project manager and double-checked by the PI prior to entering into an encrypted access database. The database will be managed by the data management team at KNCV TB Foundation in The Netherlands in line with data collected during the IMPACT-TB project. The data will be protected by KNCV on a password-secured server with availability limited to only key members of the study team when required for analysis.

### Data analysis and statistical plan

The quantitative data collected during the household visits of Project 1 will be analysed using simple descriptive statistics. Continuous costs data will be summarised by their arithmetic means and their 95% confidence intervals whether the data is Gaussian or non-Gaussian, because this approach is considered to be robust for health economics data analysis
^6,
34–
36^. Furthermore, because of the skewed nature of some expenditure data, median values may be zero or close to zero limiting the descriptive usefulness of presenting median values. As described in the PI’s previous research
^6^, any direct expenses, lost income, or annual income recorded as “zero” or missing will be replaced with the mean cost of each costs category, i.e. mean direct costs or lost income. The local currency, Nepalese rupee, will be converted into United States Dollars (conversion rate and date estimated through
Oanda at time of data collection). Categorical data will be summarised as proportions with 95% confidence intervals.

With regards to analysis of household income and expenditure, the WHO TB Patients Costs Survey methods will be followed. In order to evaluate the optimal analytical strategy for costs data in Nepal, the analysis will compare and contrast the different approaches used in the WHO Survey to estimate household income (self-reported household consumption; self-reported household expenditure; self-reported household income; and estimated income based on household asset ownership and dwelling characteristics) and lost income (output approach of reported income pre- and during TB versus human capital approach of multiplying hours of work lost by hourly rate or daily in rate in cases of hospitalised patients).

Social determinants of TB including sociodemographic characteristics, socioeconomic position, stigma and social capital levels, and TB-related knowledge will be compared between ACF patients, PCF patients, and controls using Chi-squared test, Pearson’s test, one-way ANOVA, and multiple logistic regression models where appropriate. No comparison will be made between patients and controls concerning healthcare expenditure as this data was not collected from controls. Statistical analysis will be performed using the statistical software package STATA v13.1 (Statacorp, TX, USA).

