### Primary aims

The primary aim of Project 1 is to evaluate the socioeconomic impact on TB-affected households of accessing and engaging with TB diagnosis and care in Nepal and compare that impact in people with TB identified through standard passive case finding (PCF) versus ACF. The primary aim of Project 2 is to collaborate with key stakeholders in Nepal to create a shortlist of potentially feasible and locally-appropriate socioeconomic interventions to mitigate this impact.

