### Study setting

The study will take place within the infrastructure of the larger IMPACT-TB study, which works with a well-established international non-governmental organisation, Birat Nepal Medical Trust (BNMT), to implement ACF activities including sputum-microscopy camps and roll-out of GeneXpert OMNI in four intervention and two control districts (with PCF only). The four districts are located in the central development region of Nepal and were selected for the IMPACT-TB project based on comparable populations and TB case detection rates (
Figure 2).

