### Study population

***Participant identification, recruitment and follow-up***. During Project 1, approximately 200 people with TB (cases) consecutively recruited to Work Package 3 (WP3) of IMPACT-TB (Health Economic Analysis) in the four study sites will be further recruited to this study. 100 of these cases will have been diagnosed through ACF and 100 diagnosed through PCF. Whilst attending the NTP TB clinic, these people with TB will be invited to participate in this mixed-methods research with a separate written, informed consent (see Project 1 Interview Patient Consent Form,
*Extended data*)
^29^. During months three and six of their TB treatment, household visits will be conducted by BNMT project staff including community mobilisers.

Concurrently, 100 people without TB from the study sites (controls) will be invited to participate with written, informed consent (see Project 1 Interview Healthy Control Consent Form,
*Extended data*)

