### Study interventions

The study will not include any interventions or require any patient samples (e.g. blood / sputum / tissue).

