### Study activities

Broadly, the activities involved in the research will include interviews with Cases and Controls during household visits, and a pre-FGD survey, FGD, and workshop with key stakeholders.

During Project 1, the project team will support BNMT district coordinators, community mobilisers, and community volunteers to do household visits to approximately 200 Cases with TB (100 diagnosed through ACF and 100 through PCF) recruited to WP3 of the IMPACT-TB project. People with TB will receive two household visits, the first during month three of TB treatment and the second visit during month six of TB treatment (to correspond with treatment completion). For controls, a single household visit and interview will be done. The interviews will be structured (see Project 1 Interview,
*Extended data*)
^29^ and gather data on: i) socioeconomic position, evaluated by a multi-dimensional poverty score
^6,
9,
13,
15^ assessing dwelling characteristics, assets, and access to amenities; ii) household structure, including distribution of age, sex, and employment of household members; iii) food expenditure and security; iv) costs of engaging with TB care including direct costs (e.g. medicines, clinic visits, food, and travel) and indirect costs (e.g. lost income), which will be evaluated using an adapted version of WHO’s TB Patient Costs Survey integrated into the interview
^22,
23^; v) coping strategies including dissaving (e.g. selling assets), schooldays lost, and temporary income-generating activities; vi) TB-related knowledge including understanding of transmission, prevention, and treatment of TB; vii) psychosocial situation evaluated through questions relating to social capital, quality of life, and stigma (Controls without TB will not be asked any questions about the impact that having TB disease has on their psychosocial situation); and viii) access and uptake of existing social protection schemes (whether TB-specific or TB-inclusive) and support for TB-affected households, evaluated through use of both closed ranking and open free-text questions to establish what socioeconomic and other support people with TB and their households receive or would like to receive.

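### The ACF-versus-PCF cost comparison in Project 1's primary aim is planned only as crude group summaries, with no adjustment for who each route reaches

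*Protocol article*

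**What the plan says.** The Primary aims section sets out to evaluate the socioeconomic impact of accessing TB care and to "compare that impact in people with TB identified through standard passive case finding (PCF) versus ACF". The Outcomes section repeats this comparison, and the Discussion presents it as the first known one of its kind. Cost is a central part of that impact: the Study activities section collects "costs of engaging with TB care including direct costs (e.g. medicines, clinic visits, food, and travel) and indirect costs (e.g. lost income", among other items.

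The groups are formed by how patients happened to be diagnosed. The Study population section plans for "approximately 200 people with TB (cases) consecutively recruited to Work Package 3 (WP3) of IMPACT-TB", of whom "100 of these cases will have been diagnosed through ACF and 100 diagnosed through PCF". The Study interventions section adds: "The study will not include any interventions".

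The Data analysis and statistical plan opens with "The quantitative data collected during the household visits of Project 1 will be analysed using simple descriptive statistics". It then fixes arithmetic means with 95% confidence intervals for costs and proportions with 95% confidence intervals for categorical data. Chi-squared and Pearson's tests, one-way ANOVA and multiple logistic regression are named for ACF patients, PCF patients and controls. They are attached to social determinants: sociodemographics, socioeconomic position, stigma, social capital and TB knowledge. Costs, lost income and catastrophic cost do not appear in that list.

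**The concern.** The secondary aim receives comparative tests and models, while the cost contrast in the primary aim receives none. This matters because the protocol supplies the ingredients of confounding. The Introduction reports that patients who are poorer, migrant or rural bear a disproportionate share of total costs. The Study setting section describes ACF as outreach that includes sputum camps, which may reach a different mix of people from those who present themselves. The analysis section will even test whether ACF and PCF patients differ in socioeconomic position, yet nothing carries such a difference into the cost comparison.

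If ACF reaches poorer households, a crude contrast could hide a real saving from ACF. If it reaches better-off households, it could create an apparent one. The Dissemination section intends the findings for peer-reviewed papers and for feedback to the National TB Programme and WHO, so readers are likely to take the contrast as telling them something about case-finding route.

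**Working it through.** **What is fixed, set side by side**

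- Aim: compare impact, including cost, between ACF and PCF (Primary aims).
- Groups: 100 ACF and 100 PCF, not allocated (Study population; Study interventions). 100 + 100 = 200, which agrees with the stated number of cases.
- Method for mean cost: group means with 95% intervals (Data analysis and statistical plan).
- Methods for group comparison: the tests and regression above, attached to social determinants.
- Of the named methods, one-way ANOVA would be an unadjusted comparison, and logistic regression does not apply to a continuous cost. No named method therefore adjusts mean cost.

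The plan gives no SD, effect size, alpha or power, so there is no powered figure to reproduce. What follows is illustration: n = 100 per group comes from the protocol and the other inputs are assumed.

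**Precision of the mean difference.** In SD units the standard error is sqrt(2/100) = 0.141, so the 95% half-width is 1.96 × 0.141 = 0.28 SD.

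**Effect of an unadjusted shift.** Suppose route has no true effect, but differences in patient mix shift the mean by b SD. The chance that the unadjusted 95% interval excludes zero is 1 − Φ(1.96 − b/0.141) + Φ(−1.96 − b/0.141):

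| Assumed b (SD) | Chance of excluding zero |
|---|---|
| 0 | 5% |
| 0.1 | 11% |
| 0.2 | 29% |
| 0.3 | 56% |
| 0.4 | 81% |

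**The same on the catastrophic-cost scale** (above 20% of annual household income, as defined in the Introduction). The bias in the risk difference is the difference in prevalence of the confounder times the difference in risk that it carries. Suppose ACF patients are 20 to 30 percentage points more often poor, and catastrophic cost is 30 to 40 points more frequent among the poor:

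- low end: 0.20 × 0.30 = 0.06
- high end: 0.30 × 0.40 = 0.12

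At an assumed 50% risk, the 95% half-width is 1.96 × sqrt(2 × 0.25/100) = 0.139. Confounding of 6 to 12 points is thus about 43% to 87% of the half-width (0.06/0.139 and 0.12/0.139). A bias of that size could conceal or imitate an effect that the study might otherwise hope to see.

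**The case against.** Four arguments can be made for the plan.

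*The analysis section can be read more generously.* The list of social determinants is introduced as inclusive. The sentence after it rules out a comparison of healthcare expenditure only between patients and controls, which may imply that costs are compared between ACF and PCF. That reading is possible. Logistic regression could then serve for catastrophic cost, but mean cost would still have no adjusted method.

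*The study is exploratory and observational.* It says that it compares, not that it estimates an effect of ACF, and the future trial concerns socioeconomic support. This stands. A reader might infer that the protocol attributes cost differences causally to route, but no section says so. It lowers the weight of the point without removing it, since the contrast remains in the primary aim.

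*Covariate lists are often left to a separate analysis plan.* That is true, and their absence alone would be no finding. The point rests on what the section does fix: descriptive treatment of costs, with comparative methods placed elsewhere.

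*The size of confounding is assumed.* This also stands. The documents give no data on how ACF and PCF patients differ.

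Three stronger readings are tempting and are not supported:

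- A reader might infer that route and district are wholly confounded. The Study setting section speaks of activities "in four intervention and two control districts (with PCF only" and then of four districts, and the Data collection section describes register data "at the intervention and control areas". But the Abstract names four districts and the Study population section recruits cases in four study sites. The second phrase may describe only the register's coverage, and the map that might settle the matter is not shown. The source of each group is unclear; confounding by district is not established.
- A reader might infer that the intervals fail because costs are skewed. Under-coverage is a matter for a single skewed mean. For the difference between two groups of 100, simulated coverage of ordinary intervals was 95% to 96% under lognormal costs, because the skewness largely cancels.
- A reader might infer that the fixed 1:1 split biases an overall mean. The plan specifies no unweighted all-cases estimate.

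**Conclusion.** The point holds in a limited form. Followed as written, the plan yields a crude cost contrast between groups that nobody allocated, for a comparison that sits in the primary aim, and the protocol's own background names factors that drive cost. Even on the generous reading, no stated method adjusts mean cost.

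The size cannot be derived from the documents. Under assumed confounding of 0.1 to 0.4 SD, the unadjusted interval would exclude zero in 11% to 81% of studies with no true effect of route. On the catastrophic-cost scale, the assumed shift is 6 to 12 points against a half-width of about 14. These figures rest on the assumed imbalances. If ACF and PCF patients turn out alike on the relevant characteristics, the crude and adjusted results will agree and little is lost. Given the exploratory purpose, this is an improvement to make before analysis and not a defect that invalidates the study.

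**What to change.** In the Data analysis and statistical plan:

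1. Keep the crude group means and add an adjusted ACF-PCF comparison of total cost, using a regression for the mean: for example a GLM with log link, or linear regression with robust or bootstrap intervals.
2. Add an adjusted comparison of catastrophic cost (above 20% of annual income) by logistic regression, reported as a marginal risk difference.
3. Adjust for district, age, sex, MDR status and socioeconomic measures that predate the illness where available, such as education and reported income before TB. Do not adjust for disease severity, since ACF aims at earlier detection. Do not adjust for assets recorded at the month-three or month-six visit either, since households may already have sold some to cope. Both may lie on the pathway from route to cost.
4. State which districts supplied ACF cases and which supplied PCF cases. If any supplied only one route, add a sensitivity analysis restricted to districts that supplied both.
5. Describe the result as an exploratory association.

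The cost is modest extra analysis and slightly wider intervals. No new data collection should be needed: the interview and the linked register should supply most of these covariates, although the article does not confirm that each one is recorded.

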## Introduction

Tuberculosis (TB) disease, which kills 1.5 million people annually, is driven by poverty
^1^. Having TB disease can also worsen impoverishment through loss of income and costs of accessing care
^2–
5^. Such costs can become “catastrophic”, leading patients to abandon treatment, develop drug-resistance, and die
^6^. WHO’s 2015 End TB Strategy advocates elimination of catastrophic costs and provision of socioeconomic support for TB-affected households
^5^. Nevertheless, there is minimal evidence concerning the ideal interventions to realise this policy change
^6–
10^. This research will generate preliminary evidence to fill this knowledge gap in a low-income country: Nepal. The findings will inform a randomised controlled trial of socioeconomic support for TB-affected households in Nepal.

Research from Peru has demonstrated that the severe socioeconomic impact of TB can lead to catastrophic costs (defined by WHO as >20% of a household’s annual income)
^6^. The same team also demonstrated that socioeconomic interventions for TB-affected households can mitigate catastrophic costs (
Figure 1a), improve TB preventive therapy uptake (
Figure 1b), and increase TB treatment success (
Figure 1c)
^11–
15^.

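### The cost rule treats a recorded zero as a missing value and replaces it with a category mean, which biases mean costs upward, distorts the ACF-versus-PCF comparison in an unknown direction, and leaves the replacement for zero annual income undefined

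*Protocol article*

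**What the plan says.** The rule is in the protocol article under Data analysis and statistical plan: "any direct expenses, lost income, or annual income recorded as “zero” or missing will be replaced with the mean cost of each costs category". The only gloss on which mean is used is "i.e. mean direct costs or lost income". The authority given is the principal investigator's previous research.

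Four other statements bear on it:

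- The sentence just before the rule defends means over medians on the ground that, for some skewed expenditure data, "median values may be zero or close to zero limiting the descriptive usefulness of presenting median values".
- The cost summary is fixed: "Continuous costs data will be summarised by their arithmetic means and their 95% confidence intervals whether the data is Gaussian or non-Gaussian".
- Under Primary aims, Project 1 is to measure the socioeconomic impact on households and "compare that impact in people with TB identified through standard passive case finding (PCF) versus ACF". Under Study population, "100 of these cases will have been diagnosed through ACF and 100 diagnosed through PCF".
- The Introduction describes catastrophic costs as "defined by WHO as >20% of a household’s annual income", which makes annual income a denominator.

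The protocol does not say whether the replacement mean is pooled or taken within the ACF and PCF groups, whether zeros enter it, or what replaces a zero annual income. The next paragraph of the same section plans to compare several ways of estimating household income (consumption, expenditure, self-report, assets and dwelling) but does not connect them to the rule.

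**The concern.** Zero is a legitimate value of a cost. Someone who paid nothing, or lost no pay, belongs in the average at zero. The rule moves that person to the average and makes no exception for a confirmed zero. Adjacent sentences then pull against each other: the first treats zeros as a real feature of the data, common enough to spoil the median, and the second removes them.

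Mean cost with a 95% confidence interval is the chosen summary, so any bias goes straight into the main cost result and into the ACF-versus-PCF comparison. The results are also meant to inform the protocol of a later randomised trial. A fuller analysis plan could add detail, but it would have to contradict this sentence to cure it.

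**Working it through.** The protocol states no figure that depends on this rule, so there is nothing of its own to reproduce. All zero shares, cost levels and income levels below are assumptions. The group size of 100 is from the protocol.

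**1. Mean cost.** Let p be the share of genuine zeros in a category and m the mean of the non-zero values.

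- True mean: (1−p)m.
- Zeros filled with the non-zero mean: (1−p)m + pm = m, an inflation of 1/(1−p).
- Zeros filled with the all-record mean: (1−p)m + p(1−p)m = (1−p)(1+p)m, an inflation of 1+p.

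| p (assumed) | all-record fill | non-zero fill |
|---|---|---|
| 0.1 | ×1.10 | ×1.11 |
| 0.3 | ×1.30 | ×1.43 |
| 0.5 | ×1.50 | ×2.00 |
| 0.7 | ×1.70 | ×3.33 |

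A category whose median is exactly zero has p of at least 0.5, so its mean is inflated at least 1.5-fold (all-record fill) or 2-fold (non-zero fill).

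**2. Confidence interval.** Simulation with n = 100 and log-normal non-zero costs (log SD 1). At p = 0.5 the standard error computed from the filled data is about 0.138, against an actual standard deviation of the filled mean of 0.306 (non-zero fill). For the all-record fill the pair is 0.144 and 0.242. Coverage of the true mean by the nominal 95% interval is about 92% when zeros are kept. Under the rule it is 90–91% at p = 0.1, 60–75% at p = 0.2 and 2–33% at p = 0.4, so the loss is small at low p and severe at high p.

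**3. ACF-versus-PCF difference.** Entries are PCF minus ACF under four readings of the replacement mean.

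| Assumed zeros; non-zero means (ACF, PCF) | True | Pooled non-zero | Pooled all-record | Group non-zero | Group all-record |
|---|---|---|---|---|---|
| 60%, 30%; 100, 100 | 30 | 0 | 13.5 | 0 | 27 |
| 60%, 40%; 100, 100 | 20 | 0 | 10 | 0 | 20 |
| 50%, 50%; 80, 100 | 10 | 10 | 10 | 20 | 15 |
| 30%, 50%; 60, 100 | 8 | 23.3 | 17.2 | 40 | 20.4 |
| 60%, 30%; 100, 80 | 16 | −10.2 | 1.6 | −20 | 8.8 |

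Worked case, second row, group all-record fill: PCF 60 × 1.4 = 84, ACF 40 × 1.6 = 64, difference 20, which equals the truth. When the groups differ only in zero share, a non-zero fill takes the difference to 0 and a pooled all-record fill multiplies it by half the sum of the two zero shares, so both shrink it. A group all-record fill multiplies it by the sum of the two shares (0.9 in row one, 1.0 in row two). In the last three rows the difference is unchanged, enlarged, reduced or reversed, depending on the reading.

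**4. Annual income.** On the literal reading, a zero income becomes a mean cost. Any cost above one fifth of that mean then exceeds 20%, so the household tends to be flagged. On the other reading the fill is mean income. Illustration: 10% of households with zero income, 30% with zero cost; other incomes log-normal with median 1000 and log SD 0.8; other costs log-normal with median 150 and log SD 1; non-zero means as fills; a zero-income household with any cost counted as above 20% in the true figure.

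- Zero-income households flagged: 70% true, 19% after filling.
- All households flagged: 33% true, 28% if only income is filled, 44% if costs are filled too.

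The 19% is sensitive to the inputs. A household with both values filled has a ratio of about 247/1377 = 0.18, just under the threshold.

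**The case against.** **High zero shares are not shown where the rule acts.** The gloss on categories can be read as broad totals. Under Study activities, direct costs combine medicines, clinic visits, food and travel, so a zero total should be rarer than a zero item. The remark on medians covers only some expenditure data and says they may be near zero. This stands as a limit on size: a reader might infer that much of the data would be rewritten, or that interval coverage collapses, but both need zero shares that the protocol does not give. It does not change the direction of the bias. Lost income looks the more exposed category.

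**The rule follows earlier work, and some zeros may be unrecorded answers.** The protocol never says that recorded zeros are suspected non-response, and precedent does not turn an observed zero into a missing value. Comparability with the earlier study is a fair reason to show the old rule alongside, not to make it the main analysis.

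**The rule need not shrink the ACF-versus-PCF difference.** A reader might infer shrinkage on the view that people found by outreach have more zero costs. The protocol gives no zero share for either group, and the table shows movement both ways. Only distortion of unknown direction is supported.

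**The rule need not hide the poorest.** A reader might infer this from the income replacement, or infer that with 10% zero-income households up to 10 percentage points of catastrophic-cost prevalence vanish. Both need a mean-income fill that the text does not state, and the second ignores the simultaneous inflation of costs. The 20% threshold is also given as background in the Introduction; neither the aims nor the listed outcomes name it.

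**The study is exploratory and mainly descriptive.** That excuses the absent power calculation. It does not excuse a biased descriptive mean, though it does argue against insisting on one particular imputation model.

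**Conclusion.** The rule is wrong as written and should be changed before analysis. If any recorded zero is genuine, mean costs are biased upward, by 1+p or 1/(1−p) according to which mean is used. Only the size depends on p, which is assumed here. The confidence intervals treat filled values as observed and are too narrow for that reason as well.

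The primary ACF-versus-PCF cost comparison is distorted. It moves towards zero when the groups differ mainly in zero share and the fill is pooled or the non-zero mean; otherwise it can stay put, grow or change sign. The annual-income part of the rule is not usable as it stands: literally it inserts a cost, and if mean income is meant, households with no income receive an average denominator. The share above 20% could then be wrong in either direction. The documents support no firmer statement than that.

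**What to change.** In Data analysis and statistical plan:

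1. Delete zero from the replacement rule and analyse recorded zeros as zeros.
2. Replace only missing values, by a method that carries the imputation uncertainty into the confidence intervals. Multiple imputation is one option; the exact model is the investigators' choice. State whether imputation is within or across the ACF and PCF groups.
3. Where self-reported annual income is zero, use the expenditure- or asset-based estimate that the section already plans.
4. If comparability with the earlier study is wanted, report the zero-replaced result only as a labelled sensitivity analysis.

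The cost is a few sentences and some code. Study status puts the start of analysis in February 2020, with household data nearly complete, and no new data collection is needed. The price is lower headline mean costs wherever genuine zeros occur, and less direct comparability with the earlier study.
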